## Acronyms

---

ART: Antiretroviral therapy

FPD: Foundation for Professional Development

HIV: Human Immunodeficiency Virus

HTS: HIV Testing Services

YCN: Your Care Network

## Study Summary

---

**Background:** Increasing the utilization of HIV services among people living with HIV (PLHIV) and individuals at high risk of HIV exposure is essential for ending the HIV epidemic in South Africa. There is low uptake of HIV testing services (HTS) by uninsured people at the contracted General Practitioner Care Cell (GPCC) sites who provide HIV tests. The GPCC is a well-functioning National Health Insurance (NHI)-aligned demonstration programme which aims to expand access to HIV testing services (HTS) and antiretroviral therapy (ART) for uninsured PLHIV by leveraging the capacity of private general practitioners (GPs) outside of public sector health facilities in a controlled manner. There is a social media campaign called Your Care Network (YCN), but it is not sufficient for promoting utilization of HIV services at GP practices that are nearby individuals' homes and workplaces. Although the GP care cell (GPCC) programme offers a standardized Your

Care Network (YCN) demand creation package, GPs are expected to generate HTS demand independently. Many GPs do not invest in community demand creation at their practices as the immediate benefits to the practice are not clear and they have limited expertise in community outreach. In addition, individuals may not be aware that GPs who participate in the GPCC programme offer free HIV testing services. By using behavioural insights to promote the availability of free HIV services, it may be possible to increase uptake of HTS at GP practices.

**Objectives:** To determine whether HTS demand creation material that leverages behavioural science principles will increase the demand for HIV testing at GP practices.

**Approach:** A randomized controlled trial to rapidly test two different low-cost demand creation interventions among adults residing in the catchment areas of GPCC programme clinics. For one group of participants, free HIV testing will be bundled with other health services that might be desired. Participants will receive a brochure that advertises the opportunity to receive free blood pressure testing and rapid glucose testing along with free HIV testing. This approach seeks to address stigma associated with HIV testing while also offering other health services that people value. For a second group of participants, the value of HIV testing will be emphasized using a 100 Rand voucher (US\$ 7) that can be redeemed for free services. This approach highlights the monetary value of the free services and seeks to leverage an endowment effect and loss aversion. A third group of participants will receive the standard of care promotion materials for HIV testing. The primary outcome will be presentation at the GP practice. Secondary outcomes will include HIV testing uptake, yield of new HIV-positive diagnoses, and yield of PLHIV who initiate ART. The study will be conducted at approximately five YCN GP practices in the Johannesburg Health District. We will seek to enrol 12, 000 adults in the vicinity of the GP practices who are willing to engage with a YCN field worker and willing to accept an envelope that contains one of the three HIV testing promotion strategies. The study duration will be approximately 10 months.

**Significance:** The standard marketing material (YCN brochure) and the YCN social media campaign have had limited success in increasing demand for HIV services offered by GP practices. There is a growing body of evidence from behavioural science showing that individuals' decision-making can be affected by the way in which information is presented and services are offered. We seek to test low-cost, easy-to-implement, demand creation strategies that can be implemented by the GPCC to increase demand for HIV services at GP practices.

## **1. BACKGROUND**

---

### **1.1 The HIV Care continuum in South Africa: where are the gaps?**

South Africa has built the world's largest HIV treatment program since starting to provide antiretrovirals in 2004. In 2020, there were an estimated 7.6 million people living with HIV (PLHIV) and 5.2 million (70%) were receiving antiretroviral therapy (ART) (1). Yet South Africa, like many countries, did not manage to reach the 90-90-90 targets by 2020 and is unlikely to reach the 95-95-95 targets by 2030 without further progress in expanding the utilization of HIV services. According to UNAIDS, 92% of PLHIV South Africans knew their status in 2020 but of those only 70% initiated treatment and of those 64% were virally suppressed (1). The General Practitioner Care Cell (GPCC) is an innovative, public-private partnership that seeks to increase coverage of ART among PLHIV by leveraging the resources in the private healthcare sector to reach uninsured individuals who are not accessing care.

### **1.2. The GP Care Cell (GPCC) programme**

The General Practitioner Care Cell (GPCC) is a well-functioning National Health Insurance (NHI)-aligned demonstration programme which aims to expand access to HIV testing services (HTS) and antiretroviral therapy (ART) for uninsured people living with HIV (PLHIV) by leveraging the capacity of private general practitioners (GPs) outside of public sector health facilities in a controlled manner. The GPCC is a structured network of GP practices and community pharmacies that are organised and managed to deliver HIV testing and treatment services (HTS) using the purchaser-provider split as envisioned under the NHI. The goal of this programme is to implement a private sector contracting model that achieves good HIV patient outcomes and that is rapidly scalable, highly compliant with governance criteria, low risk and a relatively low administrative burden for government and the contracted service providers. The GPCC has been operational in Gauteng Province since May 2018.

The GPCC is funded by Anova Health Institute through USAID/PEPFAR funding for

implementation in Johannesburg Health District and has been prescribed ambitious HIV Testing Service (HTS) and antiretroviral treatment (ART) initiation targets for year one as a prerequisite for securing longer-term funding. The GPCC offers a contracting solution for (1) clinical management, (2) network management, (3) stock logistics and control, (4) financial administration, and (5) M&E. The programme currently offers HTS and ART within a private healthcare setting (GP practice) to individuals for no charge at the point of care; costs of the programme are covered by PEPFAR and drugs and laboratory tests are provided by the South African National Department of Health. This has been shown to be an extremely effective way of delivering HIV treatment, but it relies on the GP practices being able to have access to the appropriate patient population and getting new individuals into the practice to test.

### **1.3 Demand creation for the GP Care Cell programme**

Currently, the GPCC offers no standardized demand creation package and GP practices are expected to create demand for these covered services themselves. There is a social media campaign called Your Care Network (YCN), but it is not sufficient for promoting utilization of HIV services at GP practices that are nearby individuals' homes and workplaces. Based on experience by the Foundation for Professional Development (FPD), contracted private sector GPs are not accustomed to mobilizing demand for their services at the community-level. The GPCC program is new and largely unknown by communities in the GPs' catchment areas, and without a successful, feasible practice demand creation strategy, the programme will not be able to reach scale.

### **1.4 Rationale / Purpose**

The standard marketing material (YCN brochure) and the YCN social media campaign have shown limited yield in driving demand for services to the GP practice. It is possible that GPs do not invest in community demand approaches at their practices, as they may not see the immediate private good of providing HTS that may have long term consequences for individual well-being. In addition, individuals may not be aware that GPs offer free HIV testing services at their practice.

There is a vital need to develop low-cost, easy-to-implement, demand creation strategies that can increase demand for subsidized HIV services at GP practices. The interventions we propose to test in this study are motivated by behavioural science research showing that low-cost interventions that alter the way in which information is presented and services are offered can influence decision-making (2).

One insight that we leverage is that behaviours that individuals may be reluctant to undertake (e.g. HIV testing) can be motivated by bundling them with other services or items that people value. Thus we propose to offer individual free health screening that includes HIV testing as well as blood pressure and glucose screening. This also overcomes stigma associated with seeking HIV services. Another insight we use is that individuals may place have greater demand for an item or service if the true value of it is made salient and they are then given an opportunity to receive it for free. Thus, we propose to offer individuals HIV testing services in the form of a voucher that indicates the value of the service and provides a discount that makes the service free. We will compare the approaches to promoting demand for HIV services at GP practices to the standard YCN brochure that is being used to create demand. This study will be conducted in compliance with the protocol, applicable regulatory requirements, and respective IRB (Wits HREC, UPenn, BU) policies and procedures.

### **1.5 Study objectives**

To determine whether HTS demand creation material that leverages behavioural science principles will increase the demand for HIV testing at GP practices.

The primary outcome will be presentation at the GP practice. Secondary outcomes will include HIV testing uptake, yield of new HIV-positive diagnoses, and yield of PLHIV who initiate ART.

This will be a randomized controlled trial to rapidly test two different low-cost demand creation

interventions among adults residing in the catchment areas of GPCC programme clinics. There will be three study groups:

1. For one group of participants, free HIV testing will be bundled with other health services that might be desired. Participants will receive a brochure that advertises the opportunity to receive free blood pressure testing and rapid glucose testing along with free HIV testing (Appendix 1). This approach seeks to address stigma associated with HIV testing while also offering other health services that people value.
2. For a second group of participants, the value of HIV testing will be emphasized using a 100 Rand voucher (US\$ 6.67) that can be redeemed for free services (Appendix 2). This approach highlights the monetary value of the free services and seeks to leverage an endowment effect and loss aversion.
3. A third group of participants will receive the standard of care promotion materials for HIV testing. The standard of care (SOC) community demand procedure includes distributing a Your Care Network (YCN) brochure that advertises free HTS and free ART services for those that test positive (Appendix 3), a website ([www.yourcarenetwork.co.za](http://www.yourcarenetwork.co.za)), a YCN Facebook page and standard signage and posters outside participating GP practices.

We will examine the effect of demand creation interventions on the likelihood that individuals will visit GP practices and utilize HIV services. We will also examine the effect of the interventions on identification of newly diagnosed PLHIV.

## **2. METHODS**

### **2.1 Setting**

The study will be conducted at GP practices in the Johannesburg Health District that are part of the GPCC. The Johannesburg Health District consists of seven sub-regions. We will purposively select approximately five GP practices that meet the following criteria:

- (1) enrolled in the existing GP Care Cell/YCN programme;

- (2) have a low performance in HIV testing and linkage to care;
- (3) have a large catchment population to reach individuals eligible for HIV testing and linkage to care;
- (4) office space to accommodate an HTS counsellor; and
- (5) willingness to participate in the study.

Table 1 is a list of GP practices that includes the estimated sub-region population and estimated HIV prevalence per sub-region. YCN field workers are currently working in these sub-regions for the Johannesburg Health District.

Table 1: Purposively selected GP practices in the Johannesburg Health District

| Area             | Region | Sub-region | Est. sub-region pop | Est. PLHIV
Prov. Estimate (12%) |
|------------------|--------|------------|---------------------|------------------------------------|
| Johannesburg CBD | F      | 60         | 39 405              | 4 729                              |
| Soweto           | D      | 37         | 30 072              | 3 609                              |
| Johannesburg CBD | F      | 124        | 43 067              | 5 168                              |
| Hillbrow         | F      | 60         | 39 405              | 4 729                              |
| Midrand          | A      | 110        | 37 331              | 4 480                              |

## 2.2 Study participants

**Inclusion criteria:** YCN field workers will approach individuals in the catchment areas of GP practices who meet the following criteria:

- Adults ( $\geq 18$  years old)
- Willing to engage with the field worker for a few minutes to learn about GPCC
- Willing to accept an envelope containing promotion materials

**Exclusion criteria:**

- Individuals who refuse to engage with an YCN field worker

### **2.3 Study design and intervention**

We will conduct a randomized control trial to determine the effectiveness of the new demand creation materials in reaching new individuals for HIV testing and linkage to care at GP practices. Individuals will be randomized to one of the study arms and will each receive an envelope containing the relevant demand creation material for their arm. The YCN field workers will use the recruitment script (Appendix 4) to inform individuals about HIV testing services at the GP practice and distribute the envelopes in the community. The name of the GP and contact number of the GP practice will be stamped on each brochure. The three study groups will include:

**Study Group 1:** A brochure promoting a free healthy lifestyle screen which includes HIV testing. This brochure will offer individuals options for a healthy lifestyle screen (weight, height, blood pressure, rapid glucose and HIV test). This brochure will be in addition to the standard of care demand creation material.

**Study Group 2:** A patient voucher for HTS (and ART): A voucher redeemable for free services valued at ZAR100 (USD 7) for HTS and approximately ZAR5,048 (USD 337) for ART (based on eligibility). The voucher will emphasize the value of the services offered. This brochure will be in addition to the standard of care demand creation material.

**Study Group 3:** Your Care Network (YCN) brochure advertising free HTS and free ART (for those who test positive) and the name and telephone contact number of the GP practice. This approach also includes existing social media platforms.

The healthy lifestyle and the patient voucher brochures will be co-designed with the study team and key stakeholders. The study demand creation material will be prototyped as part of the existing routine GPCC programme. Revisions to the brochures will be made prior to study implementation. The brochures will be submitted to ethics for approval prior to study implementation.

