### **2. Number of people attending the GP practice**

- Demographics captured by the GP practice of the target population that attends the GP practice for HTS services (age, gender), by study group
- The following category of individuals attending the GP practice will be monitored:
  - Individuals that have a brochure & self-reports that they were recruited by a YCN field worker
  - Individuals that do not have a brochure but self-reports that they were recruited a YCN field worker using demand creation material from a specific study arm
  - Individuals that have the brochure & self-reports that someone else (friend/family) gave it to them

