**The demand creation activities involve no more than minimal risk to subjects:**

- This request for an informed consent waiver is only applicable to the individuals that the YCN field worker approaches in the field for the purposes of handing out a brochure
- During the field interaction, no personal identifying information will be collected. The distribution log (Appendix 5) that will be completed by the field worker on REDCap when interacting with an individual does not collect any identifying information. This information will only track recruitment indicators from the field
- Demand creation via printed material is a routine activity that is being implemented

already and the study poses no more than minimal risk. Individuals will all receive printed information about the services available to them, but the decision to present for those services is at the choice of the individual

- The demand creation activities involve no more than minimal risk to subjects.
- The demand creation activities could not be carried out practically without the waiver or alteration
- The waiver or alteration will not adversely affect the rights and welfare of the subjects.
- Where appropriate, the subjects will be provided with additional information about their participation
- Individuals who accept the brochure and attend the GP practice to access health services or HIV testing will be invited to sign a written informed consent. Consent will be obtained for study participation and HIV testing.

We will obtain written informed consent from the individuals that present for services at the GP practice for enrolment into the study, in order to extract the necessary data from their medical records and report on the primary and secondary outcomes (Appendix 8 & 9). Consent will be obtained for those attending the GP practice to assess medical records. Following standard GPCC practice when participants present for HTS they will be consented for the medical procedure (Appendix 7).

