## **4. STUDY TIMELINE**

The study duration will be approximately 10 months. Table 2 below provides approximate time estimates allocated to each aspect of this research study. The final timeline will vary based on factors outside investigator control (i.e. ethics; other approvals).

Table 2: Study timeline

|                                     | 2021 |    |    | 2022 |    |    |
|-------------------------------------|------|----|----|------|----|----|
|                                     | Q2   | Q3 | Q4 | Q1   | Q2 | Q3 |
| Finalisation of protocol            | X    |    |    |      |    |    |
| Sub-award process                   | X    | X  |    |      |    |    |
| Ethics (Wits HREC, UPenn & BU)      | X    | X  | X  |      |    |    |
| District Approval/Letter of support |      | X  | X  |      |    |    |
| Randomisation sequence              | X    | X  |    |      |    |    |
| Protocol training                   |      | X  |    |      |    |    |
| Prototyping of brochures            |      |    | X  |      |    |    |
| Data collection                     |      |    |    | X    | X  |    |
| Data analysis                       |      |    |    |      | X  | X  |
| Report writing & dissemination      |      |    |    |      | X  | X  |

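### A routine YCN brochure cannot be told apart at the practice from the study's control brochure, so people who were never enrolled can be added to the control count

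*Protocol*

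**What the plan says.** Protocol 2.3 defines the Group 3 material as "Your Care Network (YCN) brochure advertising free HTS and free ART (for those who test positive"), with the practice's name and number. This is not a new item. Section 1.5 states: "The standard of care (SOC) community demand procedure includes distributing a Your Care Network (YCN) brochure". Section 1.4 says the new approaches will be compared "to the standard YCN brochure that is being used to create demand". Section 3.1 adds: "Demand creation via printed material is a routine activity that is being implemented" already. Section 2.1 states: "YCN field workers are currently working in these sub-regions for the Johannesburg Health District". YCN field workers also hand out the trial envelopes (2.3 to 2.5).

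On identification, 2.4 puts the mark on the envelope. Section 2.3 describes a practice stamp on each brochure and no other mark. Under 2.5, attendees are asked how they learned of the practice and are asked for the brochure. The field record is anonymous and cannot be linked to a person. Section 2.6 defines the primary outcome for enrolled adults only. The first attendance category in 2.8 is "Individuals that have a brochure & self-reports that they were recruited by a YCN field worker".

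On the two new materials, 2.3 says: "The study demand creation material will be prototyped as part of the existing routine GPCC programme". It adds that they are revised before the study starts. Table 2 in Section 4 places "Prototyping of brochures" in Q4 2021 and data collection in Q1 and Q2 2022.

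**The concern.** The arm of an attendee is known only through what that person brings or says. For that to work, study material has to be recognisable as study material. The lifestyle brochure and the voucher are new, so in the main they identify themselves. The control brochure does not, because the same item is in ordinary use, handed out by the same kind of worker in the same sub-regions.

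Someone who received a routine YCN brochure, before or during the trial, can truthfully report having a brochure and having been approached by a YCN field worker. That person is not among the 4,000 controls, yet nothing described at the practice would show it. A person counted in this way enters the control numerator but not its denominator. The error falls on one arm, so it would shrink a real difference. With no link between field and practice records, the data described could not be used to sort it out afterwards.

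**Working it through.** **Step 1. What the practice can observe (Protocol 2.3 to 2.5, 2.8)**

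| Feature | Randomised control | Holder of a routine YCN brochure |
|---|---|---|
| Item handed in | YCN brochure | YCN brochure |
| Study mark | On the envelope, which attendees are not asked for | None |
| Practice stamp | Yes | Not stated |
| Source reported | YCN field worker | YCN field worker |
| Link to a field record | None | None |
| Enrolled (2.6) | Yes | No |

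The two differ in enrolment and in the envelope. Neither is described as being checked at the visit. The stamp might help, but it identifies a practice and not the trial, and the protocol does not say whether routine brochures carry it.

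**Step 2. The plan's own figure (2.7)**

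Inputs: 5% in control, a 2-point difference (so 7%), two-sided alpha of 0.05, and 2,400 or 4,000 per arm. With the pooled-variance normal approximation and p̄ the mean of the two rates:

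power = Φ{ [ |p2 − p1|·√n − 1.96·√(2p̄(1 − p̄)) ] / √(p1(1 − p1) + p2(1 − p2)) }

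- n = 2,400: (0.9798 − 0.6583)/0.3356 = 0.958, so power is 83.1%. The stated figure of more than 80% is reproduced.
- n = 4,000: (1.2649 − 0.6583)/0.3356 = 1.808, so power is 96.5%.

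At 4,000 per arm the target difference is 280 − 200 = 80 presenters.

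**Step 3. Misattributed presenters in the control arm**

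Let c be the number of non-enrolled people counted as controls. The documents give no value for c, so the values below are assumptions. The observed control rate becomes 0.05 + c/4,000, and the intervention rate stays at 7%.

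| c | Observed control rate | Observed difference | Power |
|---|---|---|---|
| 0 | 5.00% | 2.00 points | 96.5% |
| 10 | 5.25% | 1.75 points | 90.4% |
| 20 | 5.50% | 1.50 points | 79.2% |
| 40 | 6.00% | 1.00 point | 44.2% |
| 80 | 7.00% | 0 | difference gone |

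For c = 20: (0.9487 − 0.6710)/0.3422 = 0.812, so power is 79.2%.

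For scale, 20 presenters over five practices and 12 weeks is 20/(5 × 12) = 1/3 per practice per week, or one per practice every three weeks. It would arise, for example, from 2,000 routine brochures with 1% of holders attending (2,000 × 0.01 = 20). Both of those figures are assumed.

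**Step 4. Why one-sidedness matters**

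If 40 such people were added to each of two arms (6% versus 8%), power would still be 93.9%. The harm comes from the control brochure being the only one of the three in routine circulation.

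**Step 5. The prototype route**

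Stray prototypes would act the other way. With no true effect (5% in both arms), 20 extra presenters credited to one intervention arm give roughly a 16.9% chance of a significant excess. The documents give no number for this route either.

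**The case against.** The protocol nowhere says that holders of routine brochures are counted. Section 2.6 restricts the outcome to enrolled adults, and the 2.8 categories are process measures to be monitored, not the rule for the primary outcome. A reader might infer that carry-over does enter the arm counts. The text does not support that. It shows only that nothing described keeps such people out.

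A reader might also infer that earlier exposure to YCN brochures or prototypes biases the comparison between arms. It does not, because individuals are randomised and earlier exposure is expected to balance. It may dilute a contrast, but it favours no arm. Nor does any section say that prototypes reach the public near the five practices, and revision before the study may make leftovers recognisable.

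Some safeguards exist: the marked envelope, the question on how the person learned of the practice, and the practice stamp. Section 3.7 leaves detail to operating procedures that are not shown, and the distribution and enrolment logs are listed but not shown, so a code may exist there. Section 1.4 also reports limited yield from the YCN brochure, which argues for a small c.

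All of this stands and narrows the point. It does not remove it. Section 2.6 says who should count, but the described procedures do not let the practice apply that definition to someone holding a YCN brochure.

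**Conclusion.** The point holds as an identification gap on the control side, not as a demonstrated error in the counts. As described, a routine YCN brochure and a study YCN brochure cannot be told apart at the visit. Any resulting misattribution would raise the control rate and bias towards no effect. The size is unknown. On the assumed illustration, about 20 people (0.5% of the arm) take power at 5% versus 7% from about 96.5% to 79%, and 80 would erase the target difference. These figures assume that all misattributed people are credited to control and that the true rates are those in 2.7.

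The prototype route is secondary and rests on the protocol's silence about where prototypes go. A reader might conclude that routine hand-out has to be paused in the catchments. That does not follow: such a pause is a debatable cost to a programme with testing targets (1.2), and marking the study material deals with the main problem without it.

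**What to change.** In 2.3 to 2.5:

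1. Print an arm-specific study code or mark on every study brochure and voucher. Include any YCN brochure placed in a Group 1 or Group 2 envelope, because 2.3 says those groups receive their material on top of the standard material. Without a code, such a brochure handed in alone would read as Group 3.
2. Record the code at the practice in the screening and enrolment log.
3. State in 2.6 that a presentation counts in an arm's primary outcome only when it is tied to study-coded material.
4. Report holders of uncoded material, whether routine or prototype, separately. Report attendees with no material in a sensitivity analysis. The same code deals with leftover prototypes.

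The cost is a small printing and logging step, which has to be settled before the envelopes are filled. The price in the analysis is that some true participants who arrive without their material are left out of the primary count. The sensitivity analysis shows how much that matters, including whether it differs by arm.
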